### Analysis

The findings will be reported in accordance with the Consort Statement for Pilot and Feasibility trials [43]. A consort flowchart showing the number of patients screened, approached for participation, consented and those who eventually started treatment will be presented.

Patient follow-up period will be split in to the four phases of incremental HD regime (see Fig. 2 for phases of incremental HD). Details of dialysis treatments delivered in each phase to participants in both treatment arms will be expressed in sessions/week (frequency), minutes/week (duration), mean monthly URR and median sessional eKt/V_urea_ as well as OCM Kt/V_urea_. Given that patients in conventional HD group (historical controls) will have had more BPs and weight measurements recorded since they were on three-times weekly dialysis from the outset, their mid-week BP and weight measurements will not be used in computing these averages (to avoid regression towards mean). Weights, BPs and IDGW will be summarised as means (and SDs) for each treatment phase.

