### The intervention (the incremental HD regime)

Participants in the intervention group will receive incremental HD using a novel approach, starting therapy on twice-weekly basis with progressive increases in the duration and frequency of sessions over 15 weeks, achieving conventional treatment times by the end of this period.

The treatment delivered will comprise of a ‘start’ phase, representing just the first 2 days of dialysis (this is similar to conventional start), followed by 3 incremental phases or steps (also see Fig. 2):Start (phase 1): (first 2 days of HD): day 1, 2-h HD session; day 2, 3-h HD session.Phase 2: twice-weekly 2-h long dialysis sessions for 2 weeks.Phase 3: twice-weekly 3-h long dialysis session for 6 weeks.Phase 4: three-times weekly 3-h long session for 6 weeks.

Following this, participants will continue long-term HD as per clinical requirements. The regime includes several safety elements including frequent fluid status monitoring (through clinical examinations and bio-impedance analyses) and regular potassium testing. Clinicians and dialysis nurses can override the regime at any point if clinically indicated.

The regime tested here has been developed by the study investigators ([name], SB) in consultation with patient groups as a pragmatic way of reducing exposure to dialysis during the critical early transitional period. At the designing stage, patient engagement involved discussions with National Institute of Health Research (NIHR) patient research ambassadors for renal medicine at our centre and the members of Hull Kidney Patients Association (HKPA). In addition, a brief questionnaire was given out to 20 current HD patients to gauge their opinions on the current proposals. Patient feedback was very positive; patients particularly appreciated the focus on maintaining independence at the start of HD which they valued highly. HKPA members saw this as a much-needed advancement in dialysis therapies and felt that patients will be motivated to help. The group gave positive suggestions on how to narrow down the process of identifying potential participants e.g., by prioritising the sub-set of patients who were being referred for vascular access procedure (as they are the most likely patients to start dialysis soon). In the survey of 20 HD patients, 10 patients responded 7 of whom indicated that they would have taken part in the study if they had the opportunity.

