### Follow-up

Participants will be followed-up for 6 months from the start date of HD therapy (see Fig. 1 above). A total of eight study visits will be carried out for each participant as per the schedule presented in supplementary table S1. Participant monitoring, and data collection is more intense in the first 2 weeks.

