#### Weights and blood pressures

Weight and blood pressure (BP) readings will be monitored at baseline and then at each subsequent dialysis visit. These will be measured pre- and post-dialysis. Inter-dialytic weight gain (IDWG) or loss will be recorded. BP readings taken during dialysis (intra-dialytic BPs) will also be recorded.

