#### Blood tests

In routine dialysis practice, the drawing of ‘monthly bloods’[26] involve regular measurements of full-blood count (FBC), serum biochemical profile (BCP) and C-reactive protein (CRP), and 3-monthly measurements of serum Ferritin, Transferrin Saturations (TSAT) and Parathyroid hormone (PTH) levels. We will utilise these routine tests when making selected comparisons between patients in the two treatment arms (see outcomes). Bloods samples are drawn at the first dialysis session of each calendar month. Urea reduction ration (URR) and eKt/V_urea_ are calculated monthly using the pre- and post-dialysis serum urea levels [27].

Additional (non-routine) pre-dialysis BCP testing will be carried out on days 7, 10 and 14 of dialysis to ensure close monitoring of serum potassium levels during the first 2 weeks of treatment.

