What changes, if any, do you think we need to make to the dialysis programme (the ‘incremental dialysis’) itself?	In incremental dialysis, you initially receive treatment twice weekly at shorter durations than usual, then your treatment is increased gradually over 3 months. I would like to get your thoughts on this programme: When you first started dialysis, did you notice an immediate change in how you felt? Were your symptoms changing with increasing dialysis (for better or worse)? You are now on three-times weekly full-length dialysis. With hindsight, did you have any symptoms previously that you think could have been because of less frequent dialysis?
The study included several additional procedures and tests that are not offered routinely to dialysis patients (these included questionnaires and urine collections). How did you find completing those tests?	Anything to report for the 24-h urine collections? Anything to report for the quality of life questionnaires? In future studies, should these tests be conducted more often, less often or at the same number of times as in this study?
Would you suggest we did anything differently in this study?	What changes do you think we need to make to the study overall to improve the incremental dialysis regime?
Would you recommend the study to other patients in future?	What advice would you give to someone who is about to start dialysis treatment and is offered a chance to start dialysis incrementally as part of a research study

All interviews will be conducted either face-to-face whilst patients receive their scheduled dialysis or over the internet video conferencing. Interviews will be conducted by a single researcher and are anticipated to last approximately 1 h.

With participants’ permission, the interviews will be recorded on an encrypted laptop or audio recording device which will then be transcribed verbatim and managed using Nvivo (QSR International, Australia). The transcripts will be anonymised, and all names will be replaced by a unique identifiers (IDs). Place or staff identifiers within the transcripts will be replaced by unit ID or staff job title. The study investigator will use inductive thematic analysis [45] to code the interview transcripts and then clustered into themes, along with anonymised quotes to support the account, will be presented in the final report.

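### The four regime phases end by about week 15, so the analysis by phase leaves 42–45% of the 6-month follow-up in no reporting period

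*Protocol article*

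**What the plan says.** All references are to the protocol article.

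- **Follow-up.** "Participants will be followed-up for 6 months from the start date of HD therapy".
- **The intervention.** The regime has a start phase of 2 days, then steps of 2, 6 and 6 weeks. The last is fixed in length: "Phase 4: three-times weekly 3-h long session for 6 weeks". The whole regime is said to take 15 weeks. What comes next is described separately: "Following this, participants will continue long-term HD as per clinical requirements".
- **Secondary outcomes, part A.** Blood pressure, interdialytic weight gain (IDWG), potassium, albumin, PTH, calcium, phosphate and anaemia management are to be compared between the arms over the 6-month follow-up.
- **Analysis.** "Patient follow-up period will be split in to the four phases of incremental HD regime". Delivered dialysis, weights, blood pressures, IDWG, routine bloods, IV iron and ESA doses are then summarised for each phase. No other summary is specified for these measures in that section.

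The interview topic guide (Table 3) describes the stage after the programme to participants as follows: "You are now on three-times weekly full-length dialysis".

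**The concern.** A period can be split into phases only if the phases fill it. Here they end well before 6 months, and the dialysis that follows is not one of them. The text does not say that the later weeks are excluded, but the split it sets out gives them nowhere to go.

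The analyst is left with three choices, each with a drawback:

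- **Follow the split literally.** The later weeks drop out, and a comparison defined over 6 months stops at about week 15.
- **Pool the later weeks into Phase 4.** The column then mixes a 6-week step of three 3-hour sessions a week with a longer stretch of clinically determined dialysis. It no longer shows how that step was delivered or tolerated.
- **Report one 6-month mean.** The later weeks are included, but they are not separated from the steps.

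The unassigned weeks come after the incremental steps have ended, which is when a reader would look to see whether the arms have converged or still differ. The data are also meant to inform the regime for a later randomised trial, so each step needs to be readable on its own.

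**Working it through.** **Inputs**

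- Follow-up: 6 months (Follow-up section), taken as 26 weeks = 182 days.
- Phase lengths: 2 days, 2 weeks, 6 weeks and 6 weeks (intervention section).
- Stated regime length: 15 weeks (same section).
- Blood pressure and weight: "Weight and blood pressure (BP) readings will be monitored at baseline and then at each subsequent dialysis visit".
- Routine bloods: monthly. Extra biochemistry: "pre-dialysis BCP testing will be carried out on days 7, 10 and 14 of dialysis". Less frequent tests: "3-monthly measurements of serum Ferritin, Transferrin Saturations (TSAT) and Parathyroid hormone (PTH) levels".

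**The plan's own figure.** Read literally, the phases last 2 + 14 + 42 + 42 = 100 days = 14.3 weeks. If the two start sessions are given a calendar week, the sum is 1 + 2 + 6 + 6 = 15 weeks = 105 days, which is the stated total. Both readings are carried forward.

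**Follow-up in no phase** = (follow-up − end of Phase 4) / follow-up.

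| End of Phase 4 | Days left | Weeks left | Share of 182 days |
|---|---|---|---|
| Day 105 (stated) | 77 | 11.0 | 42% |
| Day 100 (literal) | 82 | 11.7 | 45% |

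Counting 6 months as only 24 weeks still leaves 24 − 15 = 9.0 weeks (37.5%) to 24 − 14.29 = 9.7 weeks (40.5%).

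**Session readings, incremental arm.** Scheduled sessions within the phases: 2 + 2×2 + 2×6 + 3×6 = 36. Assuming three sessions a week afterwards, as the topic guide implies, there are 3 × 11.0 = 33 to 3 × 11.7 = 35.1 more. The unassigned share is 33/69 = 48% to 35.1/71.1 = 49%, before any extra sessions.

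**Blood tests per patient falling in the gap (expected numbers)**

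- Monthly tests: 77/30.4 = 2.5 to 82/30.4 = 2.7, of 182/30.4 = 6.0.
- Biochemistry in the incremental arm, with the three extra early tests: 2.5/9 = 28% to 2.7/9 = 30%.
- PTH, ferritin and TSAT: 77/91.25 = 0.84 to 82/91.25 = 0.90, of 182/91.25 = 2.0.

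**If the remainder is pooled into Phase 4 (42 days).** The post-programme share of that column is 77/(77 + 42) = 65% to 82/(82 + 42) = 66%.

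The session and blood-test figures express the same 11 to 12 weeks in other units. They are not separate evidence.

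**The case against.** The best defence is that the article is a condensed account and speaks of phases only as a convenient breakdown. The secondary outcomes already set a 6-month window for the same measures, so the phase summaries could be read as added detail, with later weeks tabulated under a fuller protocol or analysis plan that is not shown. Fig. 2, to which the Analysis section refers, is also not visible and might show a maintenance step. The regime is aimed at the early weeks, which the phases do cover. With 20 treated patients, no formal tests on secondary outcomes and recruitment as the primary outcome, little depends on this.

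Part of this stands. The consequence is modest, the three-sessions-a-week assumption comes from an interview prompt and not from the prescription, and a 6-month mean would take in the later weeks.

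The rest does not remove the problem. The article does not leave the reporting periods open: it says the follow-up period itself is divided into four phases, and it fixes the last at 6 weeks. The 6-month window in the secondary outcomes sharpens the conflict, because the stated split cannot deliver that window without dropping the later weeks or stretching Phase 4. A maintenance step in Fig. 2 would be a fifth period, which is the change proposed here.

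**Conclusion.** The concern holds. As written, the four-phase split covers at most 15 of about 26 weeks and leaves 11.0 to 11.7 weeks (42–45%) unassigned for the measures summarised by phase. This rests on 6 months being 26 weeks and on the phase lengths given in the text. Only the share of session readings (48–49%) depends on the assumed dialysis frequency after Phase 4. No error in dialysis dose is claimed, because the later session length is not given.

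The scope is narrow. Recruitment and retention, the feasibility thresholds, the counts of deaths, hospitalisations, MACE, AEs and SAEs, and the time points for residual renal function, bio-impedance, NT-proBNP, KDQOL and Karnofsky are all unaffected. No data are lost. The point should be corrected because the stated rule, if followed, shortens a prespecified 6-month comparison or blurs the last step of the regime.

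**What to change.** Add a fifth analysis period, post-programme, running from the end of Phase 4 to 6 months, and keep Phase 4 to its 6 weeks. State the cut-points in days from the start of HD and apply the same ones to the historical controls. For this period, report sessions and minutes per week, blood pressure, weight, IDWG, routine bloods, IV iron and ESA dose beside the four phases. Setting the cut-points also settles whether Phase 4 ends at day 100 or day 105.

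The cost is one sentence in the Analysis section and one more column in the descriptive tables. No new data are needed, since sessions and monthly bloods are recorded throughout. The drawback is that participants moved off the schedule early would be classed by calendar period and not by the phase they received, which calls for a footnote.

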#### Safety and adverse events data

There are several safety measures built-in to our incremental HD program to protect patients from the deleterious effects of a rapid decline in RRF around the time of dialysis initiation or when at least three-times weekly dialysis is needed from the start. First, we are only recruiting patient with planned out-patient dialysis start; this excludes the majority of those who develop critical or life-threatening issues related to CKD-5. Furthermore, all participants are reviewed at the start (see study procedures in supplementary table S1) to ensure safety before patients commence the program. During the program, patients receive regular visits from the study team (in the first month, five study related checks are undertaken including review by the study medic on four occasions). Also, clinicians can change the dialysis schedule e.g., offer extra dialysis or to take the patient off the program completely at any point during the study; for this reason, the mid-week dialysis slot is always kept open in case a participant needs additional dialysis. Finally, this a short incremental regime lasting just over 3 months; hence, a decline in RRF is anticipated and treatment increases are pre-emptive in this program.

Information related to adverse events (AEs) and serious adverse events (SAEs) will be recorded continuously throughout the study based on definitions presented in supplementary table S2. Routinely, all dialysis treatments are recorded in the local dialysis treatment database and a named nurse documents a narrative account of that day’s treatment making notes of any significant events. This information will be accessed by the study team and interrogated for AEs and SAEs and substantiated with information documented elsewhere in patients’ electronic health records. Compliance with the programme and adherence (or deviations) to the prescription will be monitored.

Intra-dialytic hypotension is common and affects 17% of all dialysis sessions [39]. We define IDH in accordance with the European Best Practice Guidelines [40] as a symptomatic drop in BP during dialysis of ≥ 20 mmHg in systolic or ≥ 10 mmHg in mean arterial pressures, requiring nursing interventions such as the stopping of ultrafiltration, administration of saline or moving patients to Trendelenburg position. IDH events are recorded in the nursing entries as above which will be used as a basis for coding this information.

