### Secondary outcomes

The secondary outcomes of this study are grouped in to following sub-categories:

A. Safety outcomes

To compare key indicators of patient wellbeing in those receiving incremental HD and conventional care over the 6-month follow-up period:Differences in mean pre-dialysis BPs and IDWG (or loss)Comparison of pre-dialysis potassium levels, serum albumin, PTH, adjusted calcium and phosphate levels.Numbers of AEs and SAEs (based on definitions in table S2)Numbers of hospitalisationsNumbers and rates of major adverse cardiovascular events (the 4p-MACE: a composite of cardiovascular deaths, nonfatal myocardial infarctions, nonfatal strokes and hospitalisations for unstable angina) [42]Numbers and rates of all-cause mortalityAnaemia management: differences in Hb, Ferritin, TSAT and doses of IV iron and erythropoietin stimulating agent (ESA.)

B. Mechanistic outcomes

To study changes in RRF, fluid load, performance status and quality of life over 6 months in patients receiving incremental HD (incremental HD group only). All these are relative to baseline:Change in RRF using urine volume, KRU and Cystatin C levelsChange in pre-dialysis fluid load as measured using BIS and Ntpro-BNPChange in KDQOL-SF v1.3 scores (including in its sub-domains)Change in Karnofsky performance index

C. Qualitative outcomes

To explore patients’ experiences of starting HD incrementally and of participating in the current study using semi-structured interviews—see interview sub-study section.

D. Further feasibility outcomes

To acquire data needed for planning a future RCT:Progression to HD: some patients recruited for the current study may not start HD within the study period (the timing of onset of dialysis can be unpredictable). Of the patients recruited from pre-dialysis clinics, the proportion of patients progressing to receiving incremental HD within the study period will be reported. This will inform the number of additional participants needed in a future RCT and the duration of recruitment period.Completion rates of the non-routine tests namely the 24-h urine collections, BIS and the KDQOL-SF v1.3 questionnaire.

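### The control-only exclusion of mid-week blood pressure and weight readings has no phase limit, so in Phase 4 it creates a difference between two arms on the same weekly schedule

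*Protocol article*

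**What the plan says.** The Analysis section splits follow-up into the four phases of the regimen and states that "Weights, BPs and IDGW will be summarised as means (and SDs) for each treatment phase". It notes that controls have more readings "since they were on three-times weekly dialysis from the outset", and so "their mid-week BP and weight measurements will not be used in computing these averages (to avoid regression towards mean"). The rule names the controls only. It carries no phase limit and has no counterpart for the incremental arm.

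The intervention section sets the incremental arm's schedule after the two-day start:
- "Phase 2: twice-weekly 2-h long dialysis sessions for 2 weeks"
- "Phase 3: twice-weekly 3-h long dialysis session for 6 weeks"
- "Phase 4: three-times weekly 3-h long session for 6 weeks"

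The safety section adds that "the mid-week dialysis slot is always kept open in case a participant needs additional dialysis". This implies that twice-weekly patients attend in the first and last weekly slots, and that unscheduled sessions fall mid-week.

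The averages feed the first item listed under Safety outcomes: "Differences in mean pre-dialysis BPs and IDWG (or loss").

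**The concern.** Two things are wrong with the rule as written.

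First, the reason. Regression to the mean arises when patients or readings are selected because they are extreme. Having three readings a week instead of two does not do that. It changes the precision of each patient's mean and leaves its expected value alone, unless the extra readings differ systematically from the rest.

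Second, mid-week readings may well differ systematically. On three sessions a week the mid-week session always follows a short gap, so removing it gives more weight to the session after the long gap. Doing this in one arm only, while both arms share a schedule, builds a difference into the comparison. The documents say that descriptive comparisons will be examined for potential signals and that the data will be used to design the regimen for a future randomised trial. An artefact in a safety measure that flatters the new regimen is therefore worth removing, even though no test is planned.

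**Working it through.** The plan attaches no figure to this rule, so there is none to reproduce. The check is calendar arithmetic on the days since the previous session, averaged over the readings that count.

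**Inputs**
- Three sessions a week (controls throughout, incremental arm in Phase 4): gaps of 3, 2 and 2 days before the first, mid-week and last sessions. This is the usual calendar pattern.
- Two sessions a week in the first and last slots (incremental arm, Phases 2 and 3): gaps of 3 and 4 days. The slots are inferred from the mid-week slot being kept open.
- Assumptions not in the documents: gain proportional to time or to its square root; daily gain of 0.5 to 1.0 kg; a rise in pre-dialysis blood pressure of 0 to 4 mmHg per extra day.
- IDWG at the last slot is assumed to be calculated still, although it needs the mid-week post-dialysis weight. The article does not say.

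**Mean gap behind the averages**
- Three sessions, all kept: (3 + 2 + 2)/3 = 2.33 days.
- Three sessions, mid-week dropped: (3 + 2)/2 = 2.50 days.
- Two sessions: (3 + 4)/2 = 3.50 days.

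| Phase | Incremental | Control, as written | Control, all kept |
|---|---|---|---|
| 2 and 3 | 3.50 | 2.50 | 2.33 |
| 4 | 2.33 | 2.50 | 2.33 |

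**Phase 4, no true difference**
- Gain proportional to time: 2.50/2.33 = 1.071, so control IDWG is 7.1% higher. Seen from the other arm, the ratio is 2.33/2.50 = 0.933 where it should be 1.00.
- Gain as the square root of time: [(√3 + √2)/2] / [(√3 + 2√2)/3] = 1.573/1.520 = 1.035, so 3.5% higher.
- In kilograms, if proportional: 0.5 × 0.167 = 0.08 and 1.0 × 0.167 = 0.17.
- Blood pressure: 0 to 4 mmHg per day × 0.167 day = 0 to 0.67 mmHg.
- Readings lost per control: 6 of 18 over the six weeks.

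**Phases 2 and 3.** The rule narrows the gap difference from 3.50 − 2.33 = 1.17 days to 3.50 − 2.50 = 1.00 day, but does not remove it. In a week when an incremental patient has an unscheduled mid-week session, the gaps become 3, 2 and 2. That reading is kept while the control's is dropped, giving 2.33 against 2.50 days. Treating it as in controls gives 2.50 in both.

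**Number of readings.** With an assumed SD of 15 mmHg both between and within patients, the SD of patient means is √(225 + 225/18) = 15.4 with 18 readings and √(225 + 225/12) = 15.6 with 12. The count alone alters spread slightly and does not move the centre.

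**The case against.** The best defence is that the rule makes sense where it matters most. In Phases 2 and 3, which are 8 of the 14 weeks of Phases 2 to 4, dropping the controls' mid-week reading compares the same weekday slots and brings the gaps closer. That stands, and it is why deleting the exclusion outright is not advised. It does not reach Phase 4, where the arms already share all three slots.

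It can also be said that the one-sidedness in Phase 4 is partly inferred from silence: the stated reason implies that the rule should lapse there, and a condensed article may omit the limit. That is possible. But the sentence is explicit about controls and sets no limit, while the averages are reported phase by phase, so an analyst following it would drop the readings.

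Stronger readings are tempting, and the documents do not support them:
- *The rule inflates control means in every phase.* Phase 1 is two days and has no weekly pattern. In Phases 2 and 3 a reader might call the ratio of 1.50 with all sessions kept the true one, and 1.40 under the rule a masked one. At equal daily gain both ratios come only from the schedule.
- *It raises control blood pressure.* The documents give no relation between interval and blood pressure.
- *It discards a third of control readings over the whole six months.* The summaries cover the four regimen phases, and how the rule would apply afterwards is not stated.
- *It threatens the study's conclusions.* The primary outcome is recruitment, with feasibility judged on acceptance and retention. These averages are secondary and untested.

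**Conclusion.** The point holds for Phase 4. Applied as written, the rule gives two identically scheduled arms different mean gaps, 2.50 against 2.33 days, and so makes control IDWG look about 3.5% to 7% higher with no true difference. The direction needs only that gain increases with the length of the gap. The percentage depends on the shape of that increase, and the kilogram figures on the assumed daily gain. If the exclusion also made the last-slot IDWG impossible to calculate, only the 3-day gap would remain in controls, and the excess under proportional gain would be 3/2.33 − 1 = 28.6%. This is a reason to state the derivation, not an estimate of what will happen.

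In Phases 2 and 3 the exclusion is defensible but incomplete: gaps still differ by a day, and unscheduled mid-week readings in the incremental arm are not covered. The stated reason is wrong throughout. Severity is moderate to minor, because the comparison is secondary and descriptive.

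**What to change.** - Apply the same session-slot rule to both arms in every phase. From Phase 4, either keep mid-week readings in both arms (2.33 against 2.33 days) or drop them in both (2.50 against 2.50). Keeping them uses all the data.
- In Phases 2 and 3 the exclusion may stay, with unscheduled mid-week readings in the incremental arm treated as in controls.
- Compute one mean per patient in each phase, then summarise across patients. This deals with unequal numbers of readings directly.
- Report IDWG per interdialytic day alongside IDWG per session, and state how each IDWG is derived when a mid-week weight is excluded. The per-day figure removes the gap effect fully only if gain is proportional to time, so both should be shown.
- Delete the regression-to-the-mean reason. Where the exclusion is kept, give weekday alignment as the reason.

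Comparing the session after each arm's longest weekly gap is not a good substitute: in Phases 2 and 3 it would set a 4-day gap against a 3-day gap.

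The cost is a change of wording and slightly more analysis work. Weights and blood pressures are already recorded at each dialysis visit, so no new data are needed.
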